## Abstract

**Background:**

Evidence-based treatments (EBTs) are available for treating childhood behavioral health challenges. Despite EBTs’ potential to help children and families, they have primarily remained in university settings. Little empirical evidence exists regarding how specific, commonly used training and quality control models are effective in changing practice, achieving full implementation, and supporting positive client outcomes.

**Methods/design:**

This study (NIMH RO1 MH095750; ClinicalTrials.gov Identifier: NCT02543359), which is currently in progress, will evaluate the effectiveness of three training models (Learning Collaborative (LC), Cascading Model (CM), and Distance Education (DE)) to implement a well-established EBT , Parent-Child Interaction Therapy, in real-world, community settings. The three models differ in their costs, skill training, quality control methods, and capacity to address broader implementation challenges. The project is guided by three specific aims: (1) to build knowledge about training outcomes, (2) to build knowledge about implementation outcomes, and (3) to test the differential impact of training clinicians using LC, CM, and DE models on key client outcomes. Fifty (50) licensed psychiatric clinics across Pennsylvania were randomized to one of the three training conditions: (1) LC, (2) CM, or (3) DE. The impact of training on practice skills (*clinician level*) and implementation/sustainment outcomes (*clinic level*) are being evaluated at four timepoints coinciding with the training schedule: baseline, 6 (mid), 12 (post), and 24 months (1 year follow-up). Immediately after training begins, parent–child dyads (*client level*) are recruited from the caseloads of participating clinicians. Client outcomes are being assessed at four timepoints (pre-treatment, 1, 6, and 12 months after the pre-treatment).

**Discussion:**

This proposal builds on an ongoing initiative to implement an EBT statewide. A team of diverse stakeholders including state policy makers, payers, consumers, service providers, and academics from different, but complementary areas (e.g., public health, social work, psychiatry), has been assembled to guide the research plan by incorporating input from multidimensional perspective.

**Trial registration:**

ClinicalTrials.gov: NCT02543359

## Background

Disruptive behavior disorders (DBDs) affect a substantial number of young children, have lifelong implications if left untreated (e.g., [1–7]), and represent the most common presenting problem to community mental health centers [8, 9]. Meta-analytic reviews of treatment outcomes for DBDs (e.g., [10]) demonstrate that there are EBTs for DBDs. Parent–Child Interaction Therapy (PCIT) is a nationally recognized EBT for families who have children with DBDs [11]. The program is unique in comparison to other EBTs for DBDs in that it involves coaching parents as they interact with their young child (ages 2.5 –7 years). For each of two treatment phases, parents attend one didactic parent-only session during which the PCIT therapist teaches parents specific skills that will be “coached” in vivo in subsequent sessions. Parents attend approximately 12–20 weekly, 1-hour clinic-based sessions with their child [12].

Treatment outcome data from multiple randomized trials indicate that PCIT decreases child behavior problems, increases parent skill, and decreases parent stress [12–14]. When compared to waitlist controls, treatment effect sizes for PCIT range from 0.61 to 1.45 (absolute values) for parent report of child behavior and 0.76 to 5.67 for behavior observations of parent skill improvements [14]. Behavior observations indicate pre-post changes in parent behavior such as increased rates of praise, descriptions, reflections, and physical proximity and decreased rates of criticism and sarcasm (e.g., [15]). Parents report lower parenting stress, more internal (rather than external) locus of control, and increased confidence in parenting skills after learning PCIT. Parents report that child behavior improves from the clinical range to within normal limits on multiple, standardized parent report measures [15–17]. Studies have been conducted to understand the maintenance of treatment benefits [18–21], finding the majority of children (69 %) maintained gains on measures of child behavior and activity level, and over half (54 %) remained free of DBD diagnoses at 2 years post-treatment) [19].

The majority of PCIT treatment outcome studies have been efficacy trials. However, a number of effectiveness studies have also been conducted and demonstrated the positive impact of PCIT on parent, child, and family outcomes for families who complete treatment (e.g., [22, 23, 24 ]). These initial PCIT effectiveness studies also highlight some concerns when providing PCIT in community-based settings, such as higher rates of treatment attrition compared to efficacy trials.

Despite EBTs’ potential to help children and families, EBTs have primarily remained in university settings, with several reports (e.g., [25, 26]) highlighting a lack of access to EBTs in community settings. EBTs seem to be valued in frontline practice, and there is a strong push to implement them; however, the field seems to not know how best to do it, especially at scale. Billions of dollars have been invested in developing EBT implementation initiatives, yet EBTs have yet to reach their intended populations. Perhaps this is related to the lack of empirical attention devoted to training models for EBTs [27]. Little empirical attention has been paid to those who provide community care and how to effectively train them [28]. A comprehensive, recent review [28] found that three training models that are increasingly commonly used are Learning Collaborative (LC), Cascading Model (CM), and Distance Education (DE).

With the support of substantial federal funds (i.e., budgets of $29 (FY07) and $33 million (FY08)), The National Child Traumatic Stress Network (NCTSN) has focused on the implementation of EBTs [27] via the LC model. The LC approach was modeled after the Institute for Healthcare Improvement’s Breakthrough Series Collaborative Model [29, 30] for use in mental health [31]. LCs target and include multiple levels within an organization (clinicians, supervisors, senior leaders) by structuring information for specific roles. LCs can involve episodic meetings to share implementation tactics, plans, and evaluation results across multiple organizations involving several staff from each. The LC model has been implemented within healthcare for a variety of purposes (e.g., [32–36]). Within mental health, the NCTSN has used the LC method for a decade to implement several EBTs across the USA; however, there is only one published study on these efforts [37]. Four studies have been published on the use of a LC to improve engagement in mental health services [38–41] which provide primary support for initiating [38] and sustaining [39] gains in initial appointment show rates. Only one randomized controlled trial (RCT) has been completed with LCs [42], which did not find favorable results (the remaining used pre-post designs). When 44 primary care clinics were randomized to either a LC or control condition, there were few statistically and no clinically significant differences in preventive service delivery rates [42]. LCs likely are costly to implement because of the staff and coordination time required.

Cascading training models (also commonly called train-the-trainer models) have the potential to be time- and cost-effective and are widely used in mental health [43, 44], addictions [45, 46], medicine [47–53], and prevention [54–60]; however, this method has received little rigorous examination. The CM involves an EBT expert providing extensive clinical training to a community-based clinician who in turn replicates that clinical training with other clinicians within her organization. Within mental health, three early studies, two single subjects [61, 62], and one [63] quasi-experimental design, indicate a “watering down” effect from supervisors to staff [62]. In the only published RCT including CM (compared to expert and self-study) few differences were found between CM and expert training on fidelity or competence in rated client sessions. In role-played sessions, participants in the expert training condition evidenced greater gains initially; by 12-week follow-up, there were no differences across conditions in client or role-play sessions [46]. Train-the-trainer models may rely heavily on the individual trainer, making them vulnerable to that person’s turnover or change of role. The trainer may serve as a local champion for the model, potentially troubleshooting the implementations of organizational needs but not to the degree inherent in the LC structure.

DE, with strategies that include an individual’s attempt to acquire information or skills by independently interacting with training materials (e.g., computer, videotape review; not simply reading materials), are a common way clinicians learn new treatments [64], have been rated favorably by learners [65] and found to be a cost-effective method to increase knowledge [66, 67]. However, when stringent assessment methods are used, DE has been found to work only for some therapists (e.g., [68]) and to be only slightly more effective than reading written materials at improving knowledge [66, 69]. Of note, when more sophisticated online training methods are used, DE has shown favorable effects as compared to written materials or workshop training with regard to increased knowledge, competence, and fidelity. Sophisticated DE methods have the advantage of being cost-effective and the potential to make a broader public health impact given that more clinicians could access an online system than could attend in-person training. However, they may be less able to address implementation challenges beyond practitioner skill training, which LCs specifically and directly address and which CM models may indirectly address via a local trainer as EBT champion within an organization. In sum, each of these models has a distinct balance of potential strengths and limitations across dimensions of cost, effort, organizational impact, resilience to turnover, and sustainment.

## Methods/design

Within implementation science most conceptual frameworks acknowledge that implementation is a complex, interactive process in which clinician behavior (clinical practice) is influenced by individual and environmental characteristics as well as the quality of the intervention and the training design [70]. In this application (ClinicalTrials.gov Identifier: NCT02543359), we borrow from two frameworks: (1) the training transfer conceptual model [71] and (2) draft model of implementation research [72]. These frameworks were chosen because of their focus on training and transfer rather than broader competing frameworks.

Originally proposed by Baldwin and Ford [73], Ford and Weissbein [71] updated a conceptual model, the Training Transfer Conceptual Model, that was developed from an industrial/organizational psychology research review to articulate the conditions (training inputs) that impact training outcomes and training transfer (implementation). While the studies reviewed in these articles were not therapist/therapy studies, the conceptualization remains relevant. The review confirmed three types of training input factors that impact learning, retention, generalization, and maintenance of skills: trainee characteristics, training design, and work environment. In this study, the experimental manipulation has been at the Training Design level. The outputs of learning and retention are operationalized to include knowledge, skills, and attitude [74]. Transfer conditions include generalization and maintenance, which in this case, would include how clinicians apply the EBT in their setting and with families they treat (i.e., implementation and client outcomes).

Proctor and colleagues [72] have proposed a heuristic model that accounts for intervention strategies (EBT), implementation strategies (i.e., training models), and three distinct but interrelated set of outcomes within implementation research: implementation, service, and client outcomes. Using this taxonomy, we will use one intervention strategy (PCIT) to test three different training designs (LC, CM, DE) and will measure implementation and client outcomes to understand the conditions of transfer (generalization and maintenance). To understand the effectiveness of training methods, we will also measure training outcomes (outputs) articulated by Ford and Weissbein [71]. Measuring both implementation and client outcomes will help us to understand the success of the training condition for implementing an EBT in community settings [75]. Training outcomes (clinician level) are assessed using observational and self-report methods at four timepoints coinciding with the training schedule: baseline, 6 (mid), 12 (post), and 24 months (1 year follow-up). Immediately after clinician training began, parent–child dyads are recruited from the caseloads of participating clinicians. Client outcomes (parent–child dyad level) are assessed by parent report at four timepoints (pre-treatment, 1, 6, and 12 months after the pre-treatment). Implementation outcomes [75] (clinic level) are assessed using behavior observation, interview, and self-report measures with administrators, clinicians, and families at baseline, 6 (mid), 12 (post), and 24 months (1 year follow-up). This will include examining the overall penetration of the EBT (e.g., how extensively it is used) and whether the EBT is able to be diffused through the organization and sustained over the course of the study.

### Participants and enrollment procedures

#### Clinics

Highlighted in Fig. 1 (clinical enrollment flowchart), there are 508 licensed, psychiatric outpatient clinics across Pennsylvania. Given concerns about contamination across study condition, if one organization operated in multiple counties (e.g., an organization had outpatient clinics in neighboring counties), the organization was only able to participate in one county. This eliminated 201 clinics from inclusion. We excluded clinics that did not treat young children (eliminating 73 clinics), had previously participated in PCIT training (eliminating 33 clinics), and had a restricted service population (e.g., specialized in treating developmental disabilities or trauma; eliminating 34 clinics).

**Fig. 1 Fig1:**
[figure not shown]
Clinic enrollment flowchart

Because we randomized at the county level, we had to approach county administrators before clinic administrators. All 67 counties were approached; 40 agreed to informational meetings. Because 27 counties did not agree to informational meetings, 73 clinics were not given the opportunity to participate. Of the remaining 94 clinics eligible for participation, 50 agreed to participate. With the support of the state children’s mental health office, we gathered data on the clinics that were not interested in participating to understand potential selection bias (e.g., clinic size, population treated, county).

To be enrolled, clinics also met the following criteria: (a) willing to participate in PCIT training, (b) able to cover site preparation costs, and (c) agreeable to research participation.

#### Administrators

To be eligible, administrators were employed at a clinic selected to participate in training as an Executive Director, Chief Financial Officer, or other person responsible for daily operations.

#### Clinicians

To be eligible, clinicians were (a) currently employed at a clinic selected to participate in training, (b) a masters or doctoral level professional in the human services field (e.g., social work, psychology, education), (c) licensed in his/her field OR receiving supervision from a licensed individual, (d) actively seeing children and families who are appropriate for PCIT (e.g., age, behavior problem severity), (e) receptive to training but not previously trained in PCIT, and (f) amenable to study tasks (e.g., video taping, completing assessments).

Based on experience with implementation studies [76, 77] and high mental health workforce turnover [78, 79], we anticipated that few clinicians will leave the training or withdraw from the study (e.g., we had a retention rate of 96 % (187/195) for clinicians in a similar trial). However, we anticipate that up to 35 % of clinicians will leave their clinics (e.g., resign) or change jobs within their clinic during the course of the study [77]. Using an intent-to-train model, clinicians who leave their clinic will remain in the study, but we may lose some clinic and client level data unless the clinician goes to another clinic that is already participating in the study or providing PCIT. All efforts have been made to get full data, but clinic level ethical, fiscal, and logistical details (e.g., FWAs, IRB protocols) may prohibit full data collection at a new site.

#### Parent–child dyads

Clinicians were asked to refer all families on their caseload with whom they are using PCIT. Inclusion criteria include any parent–child dyad who the clinician enrolled in PCIT services. A child is excluded only if he/she is a ward of the state or living in state custody. Under the study state’s law, only the birth parent or a guardian with parental rights can provide informed consent.

Clinicians ask each parent participating in PCIT to sign a “permission to contact form.” Clinicians fax the form to the research team. A research assistant contacts the parent to confirm eligibility, review informed consent including permission to video tape, and complete the first of four assessments. Subsequent assessments are completed via phone, paper, or online (depending on parent preference).

We anticipate an 88 % retention rate based on experience in previous trials; a minimum of 253 parent–child dyads likely will complete all four assessments. We estimate that the clinician to enrolled family ratio will be approximately 1:1 though we will try to improve that ratio. In previous trials, we had estimated a 1:2 ratio; however, given clinician turnover and other challenges, 1:1 has been a more accurate estimate for recent child-focused, community-based trials [80, 81].

To enhance participant recruitment and retention, incentives have been included at each level: (1) clinics receive free training for their clinicians as well as either a small stipend ($1000) to offset initial PCIT start-up costs (e.g., bug-in-the-ear) or a PCIT package including equipment (e.g., video cameras) necessary for the research and helpful for treatment; (2) administrators receive payment for assessment completion; (3) clinicians receive free training, Continuing Education Credits, and payment for time invested in assessment completion (not training); and (4) parent–child dyads receive payment for assessment completion. Top officials from several state offices and behavioral health managed care companies in Pennsylvania have endorsed and are substantively involved in this research, which also may positively impact participation.

#### Contact and monitoring procedures

Due to data collection occurring across levels of participants at multiple timepoints, we have implemented a variety of prompting and monitoring procedures to enhance participation. Specifically, participants are provided with choices related to the method of data collection (paper, online, or phone) as well as preferred contact method. The study team has utilized email, phone, postal mail, and text messaging to communicate with participants.

### Procedures

#### Randomization

Counties with at least one participating clinic located in the county were randomized to study condition [82]. Randomization occurred at the county level for two reasons. First, the state in which the study is being conducted is a commonwealth that is “state administered and county controlled” meaning that there is considerable variability in how counties implement mental health policies. Given that this project, like any EBT implementation, will require clinics to develop new programs and possibly rely on the larger system/context of which they are a part of, there could be substantial variability for implementation across counties. For example, establishing a referral base likely will impact implementation outcomes and will be different across counties. Given that this variability would be difficult to quantify, our goal has been to balance across conditions through the randomization procedure. Second, it is not logistically or financially possible to train all clinics at once. If we were to randomize clinics to a condition it is probable that within one county, we would have multiple training conditions occurring at different times. This could affect the previous training condition, particularly for smaller counties where clinics might have close communication or even share clinicians. Similar to previous trials that have randomized at the county level [82, 83], randomization of county to condition was balanced on key covariates including population size (urban/ rural) and poverty level [84].

Training occurred through four waves because it would be impossible to train all clinics at the same time. Given these constraints, we used SAS to write a routine for the randomization. Within training wave 1, counties were randomized to one of two conditions. Within waves 2, 3, and 4, counties were randomized to one of three conditions. The two conditions implemented in wave 1 were randomly chosen from the three conditions. The reason for this change was because wave 1 occurred early in the study when recruitment was beginning, and fewer counties had agreed to participate by study deadlines. Wave 1 included 5 clinics located in 2 counties. Wave 2 included 18 clinics located in 12 counties. Wave 3 included 13 clinics located in 4 counties. Wave 4 included 14 clinics located in 12 counties.

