### Aim 1: determine the effects of training condition (CM, LC, DE) on training outputs (i.e., clinician knowledge, skill, and attitude)

#### Analyses

We hypothesize that the greatest improvements will be found for clinicians in the CM group followed by LC, clinic staff trained by clinicians in CM and LC groups, and DE (in that order). We will use the change scores on the following Ford-Weissbein [71] training outcomes: Coaches Quiz, Competence Check, and Coach Coding. Because training is at the clinician level, we will compute the change scores for each clinician and then compare the treatments using those changes. We recognize that the clinicians are nested within organization and will include that in our regression model, along with any other covariates that are associated with outcomes. We will use the one-way analysis of variance (ANOVA) to compare the change scores between the four groups. And because we have stated an ordered alternative (e.g., CM better than LC), we will use Bartholomew’s test which is powered for ordered alternatives unlike the usual F test, which is an omnibus test. Later, we will test the cascading effect of the CM model in comparing the performance of "second generation" CM clinicians to other clinicians in other conditions (CM-generation one, DE, LC). 

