### Proposed statistical analyses

After collecting and organizing the data, we will begin with simple graphical and numerical summaries to (for example) check for unusual observations and to assess patterns of missing data. We will then address the main aims beginning with the simplest version of the hypotheses, which in this case, will typically require an ANOVA (paying attention to the nested design) to compare training conditions. We will then do a more nuanced study of the data using appropriate (e.g., linear, logistic) regression models to relate the outcomes to both features that we used to balance the randomization, covariates such as those we balance on (population size, poverty level) and other covariates that appear to be related to differences between training conditions.

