### Practical and operational issues

Although this trial offers an innovative exploration of the implementation of an EBT within community settings, this strength also brings unique challenges. The context of the current study required frequent and thoughtful consideration of the methodological challenges that real-world circumstances presented over the course of the study.

As anticipated, movement and turnover of professional participants (i.e., administrators, supervisors, and clinicians) occurred throughout the course of the study, although this movement may impact the collection of client level data; to date, the rate of staff turnover has been lower (19 % within a one year time frame) than anticipated (35 % or higher) [120, 121]. By using an intent-to-train model, the study design allows for the continued tracking of professionals, as they change employment location or status. Through this design, we are able to continually collect data on clinician use of PCIT, as well as family outcomes, regardless of staff movement. Participating professionals were not replaced at the clinic level. This allowed for data collection to remain consistent over time while providing information about the frequency and nature of staff movement occurring in community mental health settings.

Demands unrelated to the study were placed on agencies during the study timeframe. For example, agencies reported experiencing an increasing number of audits, monitoring, and site visits from payer organizations and regulating bodies. In addition, several agencies reported administrative restructuring or clinic reorganization, which often resulted in staff turnover. One clinic reported that reorganizing resulted in about 30 % of staff leaving the organization within a few weeks, which impacted the roles and demands of participating team members.

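### Counties were randomized within waves and balanced on two county covariates, but the first-step tests use neither, and the covariate rules are open-ended

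*Protocol article*

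**What the plan says.** **Allocation (Protocol article, Randomization).** "Counties with at least one participating clinic located in the county were randomized to study condition". Training ran in four waves, and allocation was done inside each. For the first, "Within training wave 1, counties were randomized to one of two conditions"; after that, "Within waves 2, 3, and 4, counties were randomized to one of three conditions". The article adds that "The two conditions implemented in wave 1 were randomly chosen from the three conditions", without naming the one left out. It also says that "randomization of county to condition was balanced on key covariates including population size (urban/ rural) and poverty level". Wave sizes are 5 clinics in 2 counties, 18 in 12, 13 in 4 and 14 in 12.

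**Analysis (Aims 1 to 3; Proposed statistical analyses; Nesting).** Aims 1 and 2 use a one-way ANOVA across groups, with Bartholomew's test where an order is hypothesized. Aim 3 uses the same methods with allowance for nesting. The section on proposed analyses puts this simple comparison first. Population size and poverty level come in afterwards, in a regression that also takes in "other covariates that appear to be related to differences between training conditions". Aim 1 separately allows organization into its regression "along with any other covariates that are associated with outcomes". The model written out under Nesting has condition, clinic, clinician and error. Wave is not named in any of these sections.

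**The concern.** Where allocation is done inside strata and balanced on covariates, the matching analysis contains those strata and covariates. Here the first test of each aim leaves them out. Two things follow for wave.

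- One condition has no wave 1 clinics, so any difference between wave 1 and later waves enters that condition's contrasts.
- Differences between waves stay in the residual although allocation within wave has largely removed them from the condition contrast. The standard error is then too large for the design.

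Differences between waves are plausible. The article reports that during the study "agencies reported experiencing an increasing number of audits, monitoring, and site visits from payer organizations" and regulators, and that commitment to the study changed over time. It gives no figures by wave.

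The second issue is how further covariates get in. One rule selects on association with outcome, the other on apparent relation to differences between conditions. Neither is confined to variables measured before training. Both let the estimate depend on choices made after seeing the data. The second could also bring in a variable on the causal path.

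**Working it through.** **1. The plan's own total.** Clinics by wave: 5 + 18 + 13 + 14 = 50, which matches the 50 under Trial status. Counties by wave: 2 + 12 + 4 + 12 = 30, whereas Trial status gives 37 randomization units. That mismatch is a separate matter; here it affects only the degrees of freedom in step 4.

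**2. Imbalance against the condition absent from wave 1.** Assumptions, since the article gives no clinic counts by condition and no wave effect: the other 45 clinics split 45 / 3 = 15 per condition, each wave 1 county went to a different condition, and wave 1 clinics differ from the rest by d SD. A condition with k wave 1 clinics is then shifted against the absent one by

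shift = d × k / (15 + k).

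| Wave 1 split | d = 0.2 | d = 0.5 | d = 0.8 |
|---|---|---|---|
| k = 3 | 0.033 | 0.083 | 0.133 |
| k = 2 | 0.024 | 0.059 | 0.094 |
| k = 4 | 0.042 | 0.105 | 0.168 |
| k = 1 | 0.013 | 0.031 | 0.050 |

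For example, 0.5 × 3 / 18 = 0.083 and 0.5 × 2 / 17 = 0.059. With a 3/2 split the shift at d = 0.5 is therefore about 0.06-0.08 SD. Over the whole table it runs from about 0.01 to 0.17 SD.

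**3. Error rate and power.** Allocation of the 30 listed counties was simulated as described: two randomly chosen conditions in wave 1, three in each later wave. Each county contributed one mean with residual SD 1 (the county SD). Wave effects were drawn with the between-wave SD shown. The test was the three-condition omnibus F test at an assumed two-sided-equivalent nominal 5%, with and without wave as a fixed effect. There were 4,000 runs per setting. Power is for one condition shifted by 1 county SD.

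| Between-wave SD (county SDs) | Null rejection, no wave | Null rejection, with wave | Power, no wave | Power, with wave |
|---|---|---|---|---|
| 0 | 4.9% | 4.9% | 57% | 56% |
| 0.5 | 3.4% | 4.8% | 50% | 56% |
| 1.0 | 1.8% | 5.1% | 34% | 54% |
| 1.5 | 0.9% | 4.8% | 21% | 55% |

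Simulation standard error is at most √(0.5 × 0.5 / 4000) = 0.8 percentage points for power. For a 5% rejection rate it is √(0.05 × 0.95 / 4000) = 0.3 points. The simulation does not cover Bartholomew's test, the fourth (second-generation) group, or adjustment for population size and poverty level.

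**4. Cost in degrees of freedom.** Wave takes 3; population size and poverty level take 2 if each is a single term. On 30 counties and three conditions, residual df fall from 30 − 3 = 27 to 27 − 5 = 22, and the critical t rises from about 2.05 to about 2.07. On 37 units the cost would be smaller.

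**5. Covariate rules against the hypotheses.** Aim 2 expects fidelity to be highest in the two more active conditions. Aim 3 names fidelity as a mediator. Fidelity would thus satisfy the rule quoted from the section on proposed analyses. Adjusting for it would remove part of the effect that Aim 3 sets out to measure.

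**The case against.** The strongest reply is that this is a condensed article with the analysis plan not shown. Its equation is offered only as an example, the simple ANOVA is only where analysis begins, and the reference to features used in balancing the randomization might be read to include wave. Part of this stands: the example does not define the final model, and a full covariate list can be left elsewhere. But the article does fix an unadjusted first step and states two selection rules. Those are choices rather than silences, and wave is never named.

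Four stronger readings are tempting, and the document does not support them.

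- *Condition is systematically confounded with calendar time.* The two wave 1 conditions were drawn at random, so there is no bias over repeated randomizations. What remains is chance imbalance in the allocation obtained. Wave 3, with 4 counties, offered all three conditions; it is small, but no arm was excluded.
- *The balancing covariates are chosen from the data.* Population size and poverty level are named in advance. Only the additional covariates are open.
- *Omitting wave inflates false positives.* The simulation shows the reverse: rejection under the null falls below 5%.
- *Fidelity will be adjusted for.* Nothing says so, and Aim 3 gives it a separate exploratory mediator analysis. The point is only that the rule as worded does not exclude it.

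**Conclusion.** The point holds at moderate severity. The first-step analyses do not reflect how counties were allocated. The resulting shift against the arm missing from wave 1 is modest, and the main cost is power, which depends on how far the waves differ. At 0.5 county SD between waves the loss is 6 points (50% against 56%); at 1 county SD it is 20 points (34% against 54%). If waves do not differ, including wave costs about 1 point. All these sizes rest on assumed wave effects, an equal split of the later clinics and a county-level F test, because the article supplies no wave effects or clinic counts by condition.

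The weakness in the covariate rules needs no such assumptions. It follows from the wording of the two rules and the article's own hypotheses about fidelity.

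**What to change.** 1. In the first model for each formally tested aim, include wave as a fixed effect together with county population size and poverty level. Apply the ordered test to the adjusted condition means. The acceptability and appropriateness rates in Aim 2, which are not formally tested, need no change.
2. Replace both open covariate clauses with one fixed list restricted to baseline variables: the baseline score where one exists, plus the terms in item 1. State that fidelity and other variables measured after randomization enter only the mediator analysis.
3. Optionally, repeat the comparison in waves 2 to 4. It adds little once wave is in the model, because wave 1 then contributes no direct within-wave contrast with the absent condition.

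The cost is analysis wording and about 5 degrees of freedom. No new data are needed. The 30 counties listed by wave should be reconciled with the 37 randomization units before the degrees of freedom are fixed.
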